### Safety considerations and adverse event monitoring

2.9

Safety protocols will be rigorously enforced throughout the trial in accordance with the latest Consensus Statement from the American College of Sports Medicine (ACSM) (23). Prior to each training session or CPET assessment, participants will undergo a mandatory health screening, including an assessment of subjective well-being (e.g., dizziness, palpitations, excessive fatigue). Capillary blood glucose measurement will be performed conditionally, specifically when participants report symptoms suggestive of acute glycemic dysregulation (e.g., lightheadedness, shakiness, or diaphoresis) or general malaise. Sessions will be postponed if a participant reports significant subjective discomfort, or if measured blood glucose levels are<3.9 mmol/L, or >16.7 mmol/L, or >13.9 mmol/L with concurrent ketonuria or symptoms of metabolic decompensation. In the event of hypoglycemia, participants will ingest fast-acting carbohydrates and undergo re-testing after 15 minutes; the session will proceed only once glucose levels have returned to a safe range. Criteria for the immediate termination of a CPET or training session will follow ACSM guidelines, including the onset of angina-like symptoms, a fall in systolic blood pressure of more than 10 mmHg despite increasing workload, an excessive hypertensive response (systolic blood pressure >250 mmHg or diastolic blood pressure >115 mmHg), severe shortness of breath, dizziness, signs of poor perfusion, clinically significant arrhythmias, or marked ST-segment abnormalities. All adverse events, including musculoskeletal injuries, cardiovascular symptoms, and any unanticipated reactions, will be documented in standardized case-report forms by the supervising clinical exercise physiologist immediately upon occurrence. An independent Data Safety Monitoring Board (DSMB), not involved in the delivery of the intervention, will adjudicate all events to evaluate severity, relatedness, and the need for protocol modification or participant withdrawal.

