### Research design

2.1

This study is a single-assessor-blind, parallel-group, two-arm randomized controlled trial. Participants will be randomly assigned in a 1:1 ratio to either a 12-week aerobic exercise group (AE group) or a non-exercise control group (Con group). Clinical assessments will be performed at baseline (pre-intervention) and at the 12-week follow-up. A detailed schedule of enrollment, interventions, and assessments is presented in **Table 1**. Considering the minimum clinically effective dose of exercise, adherence to the intervention will be defined as the completion of at least 80% of the prescribed exercise sessions. Participants who do not meet this threshold will be categorized as non-adherent. To minimize attrition bias, all participants, regardless of their adherence or completion of the intervention, will be followed up and included in the primary analysis according to the intention-to-treat (ITT) principle. Written informed consent will be obtained from all participants before enrollment. The reporting of this trial will adhere to the Consolidated Standards of Reporting Trials (CONSORT) statement.

**Table 1 T1:** Participant timeline: schedule of enrollment, interventions, and assessments.

Trial period	Enrollment		Post-randomization			Close-out
Timepoint	Screening *(Day-12 to 0)*	Baseline *(Day0)*	Intervention Period *(Weeks 1-6)*	Intervention Period *(Day42)*	Intervention Period *(Weeks 6-12)*	*Week 12 (± 3 days)*
Enrollment:						
Eligibility screen	X					
Informed consent	X					
Medical history	X					
Randomization		X				
Intervention:						
Aerobic Exercise Group		X				X
Control Group		X				X
Assessments:						
Primary outcomes						
nitroglycerin-mediated dilation		X				X
myocardial global work efficiency		X				X
Secondary outcomes						
Energy Metabolism		X				X
Peak Heart Rate (HR_peak_)		X		X		X
Traditional Cardiovascular Risk Factors		X				X
Cardiovascular & Cardiopulmonary Function		X				X
Self-reported fatigue assessment		X				X
24-hour physical activity monitoring		X				X
Circulating biomarkers		X				X
Safety monitoring						
Adverse Events		X				X

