### Intervention

2.7

The exercise intervention for the AE group is structured according to the FITT-VP principle (Frequency, Intensity, Time, Type, Volume, Progression). The protocol aligns with the American College of Sports Medicine (ACSM) guidelines for exercise in patients with T2DM (23). All training sessions will be supervised by certified clinical exercise physiologists. Considering the significant effects of AE on glucose homeostasis, all supervised sessions will be scheduled 1–2 hours postprandially to prevent exercise-induced hypoglycemia.

The exercise intervention consists of a 12-week supervised program with three sessions per week. Each session comprises a 5-minute warm-up (50%–60% of HR_peak_), 50 minutes of aerobic exercise (55%–75% of HR_peak_), and a 5-minute cool-down (50%–60% of HR_peak_). Given the progressive nature of cardiorespiratory adaptations to exercise training, the 12-week program will be divided into an initial phase (Weeks 1–6) and a secondary phase (Weeks 7–12). Cardiopulmonary exercise testing (CPET) will be performed at baseline and at the end of Week 6 to assess cardiorespiratory fitness and to prescribe exercise intensity based on the heart rate peak (HR_peak_). The HR_peak_ is identified as the heart rate corresponding to the achievement of VO_2peak_ during the CPET. For participants receiving heart rate–modulating medications (e.g., β-blockers or non-dihydropyridine calcium channel blockers) or those exhibiting chronotropic incompetence with a blunted heart rate response, exercise intensity will be prescribed using a combination of the power output (Watts) derived from the CPET and the Borg Rating of Perceived Exertion (RPE; target range 12–14). This approach ensures the delivery of a consistent and relatively moderate-intensity training stimulus. Throughout the intervention, participants in the AE group will wear heart rate monitors Polar H7 (Polar Electro, Kempele, Finland) to facilitate real-time monitoring and dynamic adjustment of exercise intensity.

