Participants assigned to the control group (Con group) will not receive any supervised or structured exercise intervention. To ensure a clear distinction from the AE group, they will be explicitly instructed to maintain their habitual lifestyle patterns throughout the 12-week study period. To objectively monitor adherence to these instructions, physical activity levels will be assessed weekly using the International Physical Activity Questionnaire (IPAQ). Any deviations from baseline activity patterns will be documented.

Throughout the 12-week intervention, all participants will be required to maintain their baseline medication regimens. Dosage adjustments will be permitted only when medically necessary for safety reasons (e.g., in cases of severe hypoglycemia or uncontrolled blood pressure), and any such modifications will be meticulously documented.

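### The only named recorder of adverse events is the exercise supervisor, whom controls have no sessions with, so harms are likely to be recorded more completely in the exercise arm

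*Protocol article*

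**What the plan says.** Section 2.9 sets the scope without limit by arm: "All adverse events, including musculoskeletal injuries, cardiovascular symptoms, and any unanticipated reactions" are covered. It then fixes recorder and timing: they "will be documented in standardized case-report forms by the supervising clinical exercise physiologist immediately upon occurrence". An independent Data Safety Monitoring Board (DSMB) adjudicates severity, relatedness and any need for protocol change or withdrawal. It is not described as collecting events.

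Contact differs by arm:

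- **Exercise arm (section 2.7).** "The exercise intervention consists of a 12-week supervised program with three sessions per week", and "All training sessions will be supervised by certified clinical exercise physiologists". Section 2.9 adds: "Prior to each training session or CPET assessment, participants will undergo a mandatory health screening".
- **Control arm (section 2.7).** Controls "will not receive any supervised or structured exercise intervention". Between visits, "physical activity levels will be assessed weekly using the International Physical Activity Questionnaire (IPAQ"). This contact is described for physical activity only; no adverse-event question is attached to it.
- **Both arms (section 2.7).** Medication changes made for safety reasons are to be documented in all participants.

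In Table 1 (section 2.1), the row "Adverse Events" is marked at baseline and at week 12, with nothing in the columns between. The two intervention rows carry the same two marks. Section 2.12 describes efficacy analyses and no between-arm test of adverse events.

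**The concern.** A recording rule that depends on one person works only where that person is present. Here the named recorder sees exercise participants three times a week and has no stated contact with controls between visits. A sprain, a dizzy spell or mild hypoglycaemia would probably reach a case-report form in one arm, while the same event in the other arm has no stated route to one.

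Two uses of the data are at stake. First, if adverse events are tabulated by arm in the trial report, part of any excess with exercise would come from the collection method. Second, the DSMB judges relatedness and the need for protocol changes. Without comparable control-arm data it has a poor background rate against which to judge events in people with type 2 diabetes who exercise. The primary outcomes, NMD and GWE, are not affected.

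**Working it through.** The article gives no adverse-event rate, safety hypothesis or safety sample size, so there is no stated figure to reproduce. The check compares the text by arm and then illustrates how unequal capture carries through.

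**Step 1. Stated opportunities to detect an event between the baseline and week-12 visits.**

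| | Exercise | Control |
|---|---|---|
| Supervised sessions with prior symptom screen | 12 × 3 = 36 | 0 |
| Exercise test (CPET) with prior screen, around day 42 | 1 | 0, or 1 if the day-42 mark for peak heart rate in Table 1 covers both arms |
| Weekly IPAQ contact | not stated | 12, on activity only |
| Safety-driven medication changes documented | yes | yes |
| Named adverse-event recorder present | yes | none stated |

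Both arms also have the screen at the baseline and week-12 exercise tests. Routine enquiry about symptoms is therefore frequent in one arm and almost absent in the other.

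**Step 2. Timing in section 2.9 against Table 1.** Read literally, two marks for adverse events do not fit recording at the moment of occurrence. But the exercise row has the same two marks although training runs throughout weeks 1–12, so a pair of marks in this table may stand for a span. The table is ambiguous and does not settle when control-arm events are collected.

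**Step 3. How unequal capture carries through.** Recorded risk = true risk × capture probability. With equal true risk in both arms, the true risk cancels:

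apparent risk ratio = capture in exercise ÷ capture in control.

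All capture values are assumptions; none is in the article. With 90% in the exercise arm:

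| Control capture | Apparent risk ratio |
|---|---|
| 90% | 0.90/0.90 = 1.00 |
| 70% | 0.90/0.70 = 1.29 |
| 50% | 0.90/0.50 = 1.80 |
| 30% | 0.90/0.30 = 3.00 |

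**Step 4. In participants, with 37 per arm (section 2.5).** Assume a true risk of 30% and control capture of 50%:

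- Exercise: 0.30 × 0.90 = 27%, or 37 × 0.27 ≈ 10.0 participants.
- Control: 0.30 × 0.50 = 15%, or 37 × 0.15 ≈ 5.5 participants.
- Spurious difference: 27 − 15 = 12 percentage points.

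If someone tested this difference at two-sided 0.05, the pooled standard error would be √(2 × 0.21 × 0.79/37) = 0.0947 and the unpooled one √((0.27 × 0.73 + 0.15 × 0.85)/37) = 0.0937. The chance of a false significant excess is Φ((0.12 − 1.96 × 0.0947)/0.0937) = Φ(−0.70) ≈ 24%. Over true risks of 10% to 40%, with the same captures, the spurious difference is 4 to 16 points and that chance about 10% to 33%.

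**The case against.** The strongest objection is that no between-arm safety comparison is planned. Section 2.12 names none, the abstract lists no safety outcome, and section 2.9 is about protecting participants. This stands. A reader might infer that a planned safety analysis is biased; the article does not support that, because it announces no such analysis. What remains is that any by-arm listing of harms, and the DSMB's view, would still rest on the same records.

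A reader might also infer that Table 1 contradicts section 2.9 and leaves controls with a single recall at week 12. Neither follows. The intervention rows share the two marks, a bar or arrow may have been lost in the table, and no section describes collection by recall.

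Nor can it be said that control-arm events go unrecorded. Medication changes for severe hypoglycaemia or uncontrolled blood pressure are documented in everyone, which covers the serious end of those events, and exercise-test visits include a symptom screen. These limit the imbalance, but they do not reach minor events or events between visits that lead to no medication change.

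Finally, an article may leave operational detail to the full protocol. That would answer a complaint about silence. Here, though, the article states scope, recorder and timing, and the stated rule can be followed between visits only in the arm that trains.

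The capture rates are assumed, and the ratios only restate them. This also stands.

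**Conclusion.** The point holds in a limited form. As written, the recording rule is likely to capture adverse events more completely in the exercise arm, apart from safety-driven medication changes and exercise-test screens. The direction is towards more recorded harm with exercise, provided that the supervisor's frequent contact does raise capture. The size cannot be derived from the article; the ratios of 1.29 to 3.00 show only how assumed differences in capture would carry through. Table 1 is ambiguous rather than contradictory. No primary outcome, sample size or announced test is affected. It should still be repaired: recruitment is under way, and events missed at the time cannot be fully recovered later.

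**What to change.** 1. Attach one scripted adverse-event question to the weekly IPAQ in controls, and ask exercise participants the same question once a week in the same words.
2. In section 2.9, name a recorder for control-arm events. This should not be one of the blinded outcome assessors, since the answers could reveal allocation.
3. Base any by-arm summary, and the comparative part of the DSMB's review, on the weekly elicited events. Report events seen or volunteered in training sessions separately.
4. Make Table 1 show collection throughout weeks 1–12 in both arms, by a bar or a footnote, in line with section 2.9.
5. Record the date of the change, because participants already enrolled will have been followed under the present rule.

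The cost is a small weekly data-collection burden and a correction to one section and one table, with no change to clinical management. The article does not say whether the IPAQ is self-completed or led by an interviewer. If it is self-completed, the question is added to the form, and someone must read the answers promptly, which is slightly more work. The change narrows the imbalance but may not remove it, since exercise participants are still prompted about symptoms before every session.

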### Primary outcomes

2.10

#### Vascular smooth muscle function

2.10.1

Vascular smooth muscle function will be assessed using the same ultrasound device (unexp18g, UNEX, Japan) following a procedure similar to that of the FMD test. After at least 15 minutes of rest, participants will receive 75 µg of sublingual nitroglycerin, and the maximal dilation of the same brachial artery segment will be measured. NMD will be calculated using the formula:

$$\text{NMD\%}=\frac{\text{maximal post-nitroglycerin diameter }-\text{ baseline arterial diameter}}{\text{baseline arterial diameter}}\times 100\%.$$

#### Speckle-tracking and myocardial work analysis

2.10.2

Two-dimensional echocardiographic images of the left ventricle—including short-axis views at the basal, mid, and apical levels, as well as apical four-chamber, two-chamber, and three-chamber views—will be analyzed using EchoPAC software (Version 203). Post-processing will be performed to obtain left ventricular global longitudinal strain (LS), circumferential strain (CS), radial strain (RS), and rotational/torsional angles. Brachial artery pressure values recorded before imaging will be entered into the software, which will automatically generate left ventricular pressure–strain loops and calculate myocardial work parameters, including global work index (GWI), global constructive work (GCW), global wasted work (GWW), and global work efficiency (GWE).

### Secondary outcome

2.11

#### Glucose metabolism

2.11.1

The following glucose metabolism parameters will be measured using a fully automated biochemical analyzer: fasting blood glucose, postprandial 2-hour blood glucose, and glycated hemoglobin (HbA1c). Blood collection and storage will be performed as previously described. Fasting glucose and postprandial glucose will be measured using corresponding assay kits, while HbA1c will be quantified via high-performance liquid chromatography (HPLC).

#### Insulin levels

2.11.2

Fasting insulin levels will be measured using a commercial enzyme-linked immunosorbent assay (ELISA) kit, following the manufacturer’s protocol. The homeostasis model assessment of insulin resistance (HOMA-IR) index will be calculated from fasting glucose and insulin values using the standard formula:

HOMA-IR=Fasting blood glucose (mmol/L)×Fasting insulin (µU/mL)/22.5

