**Methods:**

This study is a randomized, single-assessor-blind, parallel-group, two-arm controlled trial that will enroll 74 patients with T2DM. Participants will be randomly assigned in a 1:1 ratio to either a 12-week supervised aerobic exercise group (55–75% of HR_peak_, three times per week) or a non-exercise control group. The primary outcomes are the changes from baseline to 12 weeks in NMD and GWE. Secondary outcomes include key cardiometabolic indicators (energy metabolism, insulin levels), office and 24-hour ambulatory blood pressure, cardiovascular risk factors, 24-hour movement behavior, cardiopulmonary function, arterial stiffness (baPWV), vascular endothelial function (FMD), cardiac electrical activity, echocardiographic parameters, and self-reported fatigue. Additional exploratory variables include markers of myocardial injury and skeletal muscle injury, circulating markers of oxidative stress and inflammation, central fatigue biomarkers, and levels of cardiovascular-related hormones. Recruitment began in June 2025 and is currently ongoing.

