### Inclusion criteria

2.3

Participants will be eligible for inclusion if they meet the following criteria: (1) diagnosed with T2DM according to the American Diabetes Association (ADA) guidelines (19); (2) aged between 50 and 65 years; (3) a disease duration of 1 to 10 years, with a stable medication regimen (including glucose-lowering agents, antihypertensives, and statins) for at least 3 months prior to enrollment; (4) HbA1c levels between 6.5% and 11.0%; (5) absence of regular exercise habits, defined as performing less than 150 minutes of moderate-intensity physical activity per week and being categorized as having a “Low” physical activity level according to the International Physical Activity Questionnaire (IPAQ) scoring protocol; (6) ability and willingness to voluntarily participate in the exercise intervention; and (7) provision of written informed consent.

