### Statistical analysis

2.12

All statistical analyses will be performed using R software (version 4.3.1 or later; R Foundation for Statistical Computing, Vienna, Austria). For the description of baseline data, normally distributed continuous variables will be presented as 
mean±standard deviation (SD), while non-normally distributed variables will be reported as median [interquartile range (IQR)]; categorical variables will be expressed as frequencies and percentages (n, %). For the comparison of baseline data between groups, independent samples t-tests will be used for normally distributed continuous variables, the Mann-Whitney U test will be used for non-normally distributed data, and the chi-square (χ²) test or Fisher’s exact test will be used for categorical data.

Efficacy analyses will be conducted according to the intention-to-treat (ITT) principle and will include all randomized participants. Continuous outcomes, including NMD and GWE, will be analyzed using linear mixed-effects models (LMMs). To rigorously control for potential confounding, background medication use will be prespecified and included as fixed-effect covariates in the models. Medications will be categorized by therapeutic class, with binary indicators (yes/no) created for: (1) glucose-lowering agents (with separate indicators for GLP-1 receptor agonists and SGLT2 inhibitors), (2) antihypertensive medications, and (3) statins. Each LMM will incorporate group, time, and the 
group×time  interaction as fixed effects, with a random intercept for each participant to account for repeated measurements.

Sensitivity analyses will be performed using multiple imputation to assess the robustness of the findings under different assumptions regarding missing data. In addition, a per-protocol (PP) analysis will be conducted as a secondary sensitivity analysis, including only participants with an attendance rate of at least 80%. Secondary outcomes will be considered exploratory and hypothesis-generating; therefore, no adjustment for multiple comparisons will be applied. A two–tailed *P*–value < 0.05 will be considered statistically significant.

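### Fasting insulin and HOMA-IR are analysed in all participants although insulin-treated patients are not excluded, so in any who enrol these values may partly reflect the prescription

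*Protocol article*

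**What the plan says.** **Outcome.** Section 2.11.2 (Insulin levels) states: "Fasting insulin levels will be measured using a commercial enzyme-linked immunosorbent assay (ELISA) kit". It then defines the index: "The homeostasis model assessment of insulin resistance (HOMA-IR) index will be calculated from fasting glucose and insulin values", with the formula "HOMA-IR=Fasting blood glucose (mmol/L)×Fasting insulin (µU/mL)/22.5". No treatment group is set apart. The abstract names insulin among the secondary outcomes: "Secondary outcomes include key cardiometabolic indicators (energy metabolism, insulin levels". The oral glucose tolerance test (2.11.3) samples glucose only, so HOMA-IR is the only insulin-resistance index defined.

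**Eligibility.** Section 2.3 admits patients with 1 to 10 years of disease, HbA1c up to 11.0%, and background treatment described as "with a stable medication regimen (including glucose-lowering agents, antihypertensives, and statins) for at least 3 months prior to enrollment". None of the eight exclusions in Section 2.4 concerns insulin therapy. The text never names insulin as a treatment.

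**Treatment during the trial.** Section 2.7 asks participants to keep their baseline regimens: "Dosage adjustments will be permitted only when medically necessary for safety reasons". Severe hypoglycaemia is one of its examples, and changes are documented. Section 2.8 requires a 12-hour fast and has morning medication withheld before assessments.

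**Analysis.** Section 2.12 includes all randomized participants in mixed models with group, time and their interaction. Medication enters as yes/no covariates, the first being "glucose-lowering agents (with separate indicators for GLP-1 receptor agonists and SGLT2 inhibitors"). Insulin has no indicator of its own, and dose is not modelled.

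**The concern.** HOMA-IR takes measured insulin to be the patient's own. In someone who injects insulin, the measured value may include the drug, depending on the kit and the insulin type. Neither is stated. Withholding the morning dose does not deal with insulin given the evening before.

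The stated rule therefore produces a value that is hard to interpret for a subgroup that the eligibility criteria allow in. At stake is the reading of two secondary measures, including the trial's only index of insulin resistance. The co-primary outcomes, NMD and GWE, do not depend on it.

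**Working it through.** The plan gives no figure to reproduce. From the article come the HOMA-IR formula and the arm size of 37. Every glucose and insulin value, share of insulin users and frequency of dose cuts below is an assumption.

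**1. Effect on one participant's value.** Let g be fasting glucose (mmol/L), e endogenous insulin and x detected injected insulin (both µU/mL). Then HOMA-IR = g(e + x)/22.5, and the ratio to the value without injected insulin is (e + x)/e, whatever the glucose.

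| g | e | x | HOMA-IR | Ratio |
|---|---|---|---|---|
| 8 | 8 | 0 | 8 × 8/22.5 = 2.84 | 1.0 |
| 8 | 8 | 5 | 8 × 13/22.5 = 4.62 | 1.6 |
| 8 | 8 | 10 | 8 × 18/22.5 = 6.40 | 2.25 |
| 8 | 8 | 20 | 8 × 28/22.5 = 9.96 | 3.5 |

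With e = 12 the ratios for x = 5, 10 and 20 are 1.4, 1.8 and 2.7. The distortion of an individual value can be large.

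**2. Stable dosing.** If x is the same at both visits, it drops out of the change in fasting insulin. In the change in HOMA-IR it leaves x(g₁ − g₀)/22.5, which is zero unless glucose itself changes. Example: e = 8, x = 5, glucose falling from 8 to 7. The change is 4.04 − 4.62 = −0.58. Without injected insulin it is 2.49 − 2.84, or −0.36 before rounding. The difference is 5 × (−1)/22.5 = −0.22 in that participant, and it only scales a real glucose change. Stable use therefore mostly cancels in the group × time contrast. What remains is mainly noise, from variation in x between people and between visits.

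**3. Dose changes in one arm.** If a proportion p of an arm has a dose change that moves measured insulin by d at fixed glucose 8, the arm's mean HOMA-IR shifts by p × 8 × d/22.5.

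- p = 0.10, d = 2: 0.10 × 8 × 2/22.5 = 0.07.
- p = 0.30, d = 5: 0.30 × 8 × 5/22.5 = 0.53.
- 4, 7 or 11 of 37 participants with d = 5: 0.19, 0.34 or 0.53.

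If p is instead the share of insulin users and only some of them have a dose cut, the shift shrinks in proportion:

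- One quarter to one half have a cut: 0.25 × 0.07 = 0.02 up to 0.5 × 0.53 = 0.27.
- One tenth have a cut: 0.007 to 0.053.

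**4. Glucose need not stay fixed.** Start from 8 × 15/22.5 = 5.33 and let measured insulin fall by 2 after a dose cut.

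- Glucose stays at 8: 8 × 13/22.5 = 4.62, a fall.
- Glucose rises to 9.2: 9.2 × 13/22.5 = 5.32, practically no change.
- Glucose rises to 10: 10 × 13/22.5 = 5.78, a rise.

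The same dose cut can move HOMA-IR either way.

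**The case against.** **The article is condensed and never mentions insulin therapy.** Who contributes to a derived secondary index is often left to the full protocol or analysis plan, and the limit of 10 years' disease duration bears on how many insulin users would enrol. This stands as a reason for modest weight. It does not remove the point, because the article itself fixes the formula, the analysis set and a covariate list that singles out two drug classes. Together these apply the index to a subgroup for which it may not mean what it says.

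**The safeguards are real.** Stable regimens, restricted and documented dose changes, the overnight fast and the withheld morning dose all reduce the problem. They do not cover insulin from the evening before, and documentation does not change the analysis. A yes/no indicator for insulin would not be enough either, since it cannot absorb a change of dose within a person between visits.

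**A reader might infer a bias in favour of exercise.** The argument would be that hypoglycaemia is likelier in the exercise arm, so insulin doses are cut there and HOMA-IR falls without any gain in insulin sensitivity. The 0.07 to 0.53 range in step 3 might be read as the size of that bias. The documents do not support this. Read that way, the range needs every insulin user in the exercise arm to have a dose cut, no control to have one, and glucose to stay at 8 mmol/L. Section 2.7 restricts dose changes to safety reasons and times sessions after meals to prevent hypoglycaemia. A cut made because glucose was low would tend to raise glucose, which step 4 shows can cancel or reverse the shift.

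**Conclusion.** The point holds as a minor one. Insulin-treated patients are not excluded, and fasting insulin and HOMA-IR are to be analysed for all randomized participants from total measured insulin. In any insulin users enrolled, these values partly reflect the prescription to the extent that the ELISA detects injected insulin.

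On the assumed values, an individual's HOMA-IR could be inflated 1.4- to 3.5-fold. For the comparison of arms, the likely cost under stable dosing is mainly noise. Dose changes that differ between arms could bias the contrast, but neither direction nor size can be established from the article. The effect is zero if no insulin users enrol or if the kit does not read their insulin. Sections 2.12 and 4 already treat secondary outcomes as hypothesis-generating, and conclusions on NMD and GWE are unaffected.

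**What to change.** Add to Sections 2.11.2 and 2.12: *Fasting insulin and HOMA-IR are analysed in participants not using exogenous insulin at baseline; the all-participant result is reported as supportive, and any insulin started after randomization is described by arm.*

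The restriction should rest on baseline use. Requiring no insulin at week 12 as well would select on treatment received after randomization and could unbalance the arms.

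The change is one sentence and alters no eligibility rule, treatment or visit. Recruitment is still under way, so it can be fixed before results are known. The cost is fewer participants for these two exploratory measures: none if no insulin users enrol, about 7 of 74 if 10% use insulin (0.10 × 74 = 7.4), and about 22 if 30% do (0.30 × 74 = 22.2). Reporting the all-participant result alongside makes any difference visible.
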